## 8.6. Timing of interim analyses

The first interim analysis will occur when 250 patients have been followed for 90 days and have observed their 90-day PDHD. Subsequent interims will occur every 3 months until the total sample size has been enrolled, using data collected from all patients for whom days from randomization has elapsed and their 90-day PDHD has been recorded.

At each interim, response adaptive randomization (RAR) allocation probabilities will be updated according to the details described in Section 8.7

## 8.7. Randomization

Initial randomization is set so that 30% of patients are randomized to STS and 70% of patients are randomized equally to the remaining 4 arms. After a burn-in of 250 patients, RAR will begin. The allocation to STS will be maintained at 30% throughout the course of the trial. The remaining 70% of patients will be allocated to the 4 active arms preferentially based on the probability that the intervention is superior to the other active arms as defined in Section 8.4.2.

## 8.8. *Futility stopping*

The interventions selected for this proposal have been used in clinical care for other conditions (e.g., heart failure) and not shown to harm patients. Furthermore, RAR ensures that a higher proportion of patients randomized to one of the four intervention arms are randomized to the better-performing arms based on the results of the interim analyses. Thus, the likelihood of harm in our trial is low.

We considered the rare scenario that an arm performs worse than usual care, for which RAR will not change the allocation ratios. We therefore included a rule where an arm would be discontinued if the posterior probability of harm (odds ratio for home days  $< 1$ ) is  $> 90\%$ :

$$\text{Futility rule: } \Pr(OR < 1) > 0.9.$$

Based on preliminary simulations, we expect enrolling ~1200 patients before harm in this scenario is detected. Our simulations also ensured that our rule would prevent an arm to be dropped prematurely and likely to show benefit at the end of the trial.

Futility checking will occur at all interim analyses except the first to allow sufficient patient accrual into each treatment arm, preventing some probability of false declaration of futility. Futility is assessed separately for each individual care model arm. Declaration of futility for a particular arm during an interim analysis will trigger an early stopping of randomization to that arm, pending review by the DSMB. If all active arms are dropped for futility, then the entire trial would conclude early. The trial would conclude at the interim at which the final active arm was dropped. Our futility rule was selected by evaluating the operating characteristics of several rules via simulation (See Appendix, Section 12.5).

## 8.9. *Analytic approach*

Analyses described in this section pertain to the statistical analysis conducted at the conclusion of the ACCOMPLISH trial, after all data have been collected.

### 8.9.1. *Final analysis of primary endpoint*

The primary analysis of PDHD will consist of the posterior probability of superiority of each active arm over STS following posterior calculation from the model in Section 8.9.1. Success will be declared at the final analysis when all patients have observed their primary endpoint if the posterior probability of any care model relative to STS is greater than 0.991. This threshold was determined through simulation to assure the type I error is controlled at a 2.5% level. Specifically, we simulated 10,000 trials under the null scenario and find the threshold that controls overall 2.5% type I error (probability of declaring success under the null) across the simulated trial scenarios (Appendix Table 4).

We will also calculate the posterior probability that each active arm is superior to the other active arms (Section 8.4.2).

### 8.9.2. Additional analysis of primary endpoint

We will also estimate the marginalized effects of RPM low and RPM high compared to STS, and alternatively Standard team and Enhanced team compared to STS. These effects will be estimated in models blinded to one or the other intervention modality. For instance, to estimate the effects of RPM low and RPM high compared to STS, we will use the following modification of model (1):

$$\begin{aligned} \text{logit}(\gamma_{i,j}) &= \alpha_j - (X_{i1}(\theta_1 + \theta_2 X_{i2}) + \beta_1 Z_{i1} + \beta_2 Z_{i2} \\ &\quad + W_{i,COV} \boldsymbol{\kappa}) \end{aligned} \quad (3)$$

The variables,  $X_{i1}, X_{i2}$  are indicators for treatment assignment, where  $X_{i1} = 1$  when randomized to one of the 4 care model interventions and 0 when randomized to the STS arm,  $X_{i2} = 1$  when randomized to an intervention with RPM high and  $X_{i2} = 0$  for RPM low. The parameters  $\theta_1, \theta_2$  are log odds ratios for active interventions; the treatment effect for RPM low/standard is equal to  $\theta_1$ , the effect for RPM high/standard is equal to  $\theta_1 + \theta_2$ . An equivalent model will be used to estimate the effects of Standard team and Enhanced team type compared to STS.

From these models, we will estimate the posterior probability that the intervention odds ratio is greater than one, and the appropriate posterior probability of superiority comparing interventions in the same model.

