#### 8.10.2. Analysis of effect heterogeneity across pre-determined subgroups

We will conduct differential treatment effects analyses, comparing differences between RPM groups and STS across pre-specified subgroups of patient-level clinical, social, and environmental factors that could be potentially used to tailor service delivery. All analyses will be performed using a cumulative logit model for the primary PDHD outcome, including terms for treatment arm, subgroup, treatment by subgroup interactions, stratification variables, and calendar time of randomization. Subgroup variables and definitions were determined as plausibly related to treatment effect heterogeneity. Each subgroup variable will be analyzed in two ways: 1) four RPM arms kept separate; and 2) comparing standard team and enhanced team arms. Analyses will not be adjusted for multiple comparisons. Evidence of differential treatment effects across subgroup levels will be summarized using the posterior probability that interaction

terms are greater than 0. In addition, treatment effects by subgroup level will be summarized using the posterior median cumulative odds ratios from each model, and corresponding 95% credible intervals.

Subgroup definitions are as follows:

- Patient Age
  - <65 vs age ≥65
- Sex
  - Female vs male
- Race
  - White patients vs Black patients
- Chronic Condition index
  - CCI<5 vs CCI≥5
- Level of comfort with technology
  - Comfortable vs uncomfortable vs missing
- Health literacy level
  - Limited vs marginal vs adequate vs missing
- State-ranked Area Deprivation Index
  - Quartile 1 vs quartile 2 vs quartile 3 vs quartile 4 vs missing
- Location after discharge
  - Skilled Nursing Facility vs home
- Severity of illness
  - Severe (mechanical ventilation or vasopressor use during index hospitalization) vs not severe
- Discharge diagnosis
  - COVID vs Non-COVID Sepsis vs Other lower respiratory tract infection

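### The marginalized RPM-level and team effects in SAP 8.9.2 are weighted by whatever allocation the adaptive randomization produced, and their labels are wrong

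*Combined protocol and SAP*

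**What the plan says.** SAP 8.3.2 defines model (1) with a term for any RPM arm (theta1), RPM-High (theta2), Enhanced team (theta3) and their interaction (delta), so it contains all four arm effects.

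SAP 8.9.2 then asks for marginalized effects of RPM level and, separately, of team type: "These effects will be estimated in models blinded to one or the other intervention modality". Model (3), the RPM version, keeps theta1 and theta2 and drops theta3 and delta. It gives no weights and no standardization over the omitted factor. The text still says that "the treatment effect for RPM low/standard is equal to" theta1, and that theta1+theta2 is the RPM high/standard effect. It will also report "the appropriate posterior probability of superiority comparing interventions in the same model", that is, RPM-High vs RPM-Low, and Enhanced vs Standard from the mirror model.

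Under SAP 8.7, allocation starts balanced across the RPM arms: "30% of patients are randomized to STS and 70% of patients are randomized equally to the remaining 4 arms". Once adaptation begins, the 70% is "allocated to the 4 active arms preferentially based on the probability that the intervention is superior to the other active arms". Under SAP 8.8, "Declaration of futility for a particular arm during an interim analysis will trigger an early stopping of randomization to that arm". Neither rule keeps the 2x2 balanced. SAP 8.10.2 includes a subgroup analysis "comparing standard team and enhanced team arms", alongside one that keeps the four RPM arms separate.

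**The concern.** In a 2x2 with equal cells, leaving out one factor still gives roughly the equal-weight average over it. With unequal cells, the omitted factor is averaged with the weights that the trial happened to produce. Those weights depend on interim outcomes and can differ between the two levels being compared.

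The label is a separate error. With no team term in the model, theta1 is the effect of RPM-Low pooled over both teams, not of RPM low/Standard. This is so even under equal allocation.

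At stake are supplementary statements about monitoring intensity and about team type. A reader may take them as properties of the component when they partly reflect the allocation.

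**Working it through.** **1. Reproducing the plan's figures.** The appendix design was simulated with 1,000 trials per scenario: the nine-level outcome of Table 2, the two strata, 70 patients a month, a first interim at 250 complete and then every three months, adaptive randomization by probability of being best, futility at 0.9, and the stated treatment priors. The posterior was a normal approximation, without time buckets.
- Scenario 3 mean sizes for arms 1 to 4 were 127/157/158/607 (total 1498). Table 5.2 gives 128/156/157/607 (total 1498).
- Arm 4 power was 0.816 in the simulation, against 0.851 in Table 5.2.
- Analytic check: Whitehead's information for the log odds ratio is n1·n2/(3N)·(1 − Σp³). With 450 and 607 patients and Σp³ = 0.146 (baseline distribution, OR 1.5, averaged by arm size) it is 73.5, so the SE is 0.1166. Power = Φ(0.4055/0.1166 − 2.366) = 0.87.

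The allocation is reproduced closely and the power roughly.

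**2. Team mix at the Table 5.2 mean sizes.** Arms 1 to 4 are Low/Standard, High/Standard, Low/Enhanced and High/Enhanced. The Enhanced share is n4/(n2+n4) in RPM-High and n3/(n1+n3) in RPM-Low.

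| Scenario | Sizes, arms 1 to 4 | Share in High | Share in Low |
|---|---|---|---|
| 3 | 128/156/157/607 | 607/763 = 79.6% | 157/285 = 55.1% |
| 4 | 104/128/124/695 | 695/823 = 84.4% | 124/228 = 54.4% |
| 6 | 109/410/111/420 | 420/830 = 50.6% | 111/220 = 50.5% |
| 12 | 125/163/162/599 | 599/762 = 78.6% | 162/287 = 56.4% |
| 13 | 106/132/134/678 | 678/810 = 83.7% | 134/240 = 55.8% |

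**3. Effect when the factors interact.** Take the size-weighted mean of the Table 3 log odds ratios within RPM-High and compare it with a 50:50 mean.
- Scenario 3: 0.796 × ln 1.5 = 0.3226, OR 1.38. Equal weights: 0.5 × ln 1.5 = 0.2027, OR 1.22.
- Scenario 4: 0.844 × ln 1.75 = 0.4726, OR 1.60. Equal weights: 0.2798, OR 1.32.

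Both RPM-Low cells have OR 1.0 here, so these values are RPM-High vs STS and also High vs Low. In scenarios 12 and 13 the High vs Low values are again 1.38 against 1.22 and 1.60 against 1.32. In the simulation of scenario 3, model (3) gave a median High vs Low OR of 1.38, and the equal-weight contrast from model (1) gave 1.26, against a target of 1.225.

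**4. Effect when only one factor works.** A false signal is counted when the posterior probability that one level beats the other falls outside 0.025 to 0.975.
- Scenario 6 (only RPM-High works, OR 1.5), Enhanced vs Standard, true OR 1.00: pooled team model 7.3% + 8.4% = 15.7%; equal-weight contrast 1.5% + 3.2% = 4.7%.
- Mirror of scenario 6 (only Enhanced works), High vs Low, true OR 1.00: model (3) 6.2% + 9.7% = 15.9%; equal-weight contrast 2.2% + 3.3% = 5.5%; model (3) under fixed equal allocation 2.4% + 1.5% = 3.9%.

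The median pooled OR for the inert factor was 1.00 in both cases, so there is no average bias. The cause is drift within single trials. In scenario 6 the difference in Enhanced share between RPM levels had a 95% range of about −0.33 to +0.34. In the mirror case the model (3) contrast correlated 0.81 with that difference.

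**5. Global null.** For High vs Low, model (3) gave 6.5% and the equal-weight contrast 5.0%, which is within or near simulation error.

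**The case against.** A reader might infer that RPM-High vs RPM-Low is confounded with team type and that the tables show it. They do not. In scenarios 3 and 4 the two RPM-Low cells both have OR 1.0, so the team mix in RPM-Low cannot matter. The gap comes only from how an interaction is weighted within RPM-High. In every Table 3 scenario with an unequal mean team mix (2 to 4 and 11 to 13), the two RPM-Low cells share one odds ratio. Equal weighting is also a choice of target, since with a pure interaction no single component effect exists. In scenario 6, the mean team mix is balanced and the inert factor shows no average bias.

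Section 8.9.2 is also supplementary. Aims 1a and 1b concern arms, the marginal analysis has no success threshold, and model (1) reports all four arm effects beside any pooled figure. The time buckets do not answer the point, because they adjust for calendar time and not for the omitted factor.

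A reader might also carry the problem straight over to 8.10.2. No size of bias has been shown there, and the four-arm subgroup analysis is already planned.

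These objections limit the point. They leave standing the unstated, allocation-dependent weights, the wrong labels and the excess false signals in single trials.

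**Conclusion.** The point holds as a defect of a supplementary analysis. Model (3) estimates an allocation-weighted average that the SAP does not define, and the labels on theta1 and theta1+theta2 are wrong under any allocation. With interacting factors, the pooled odds ratio at the plan's own mean sizes is 1.38 rather than 1.22 (scenario 3) or 1.60 rather than 1.32 (scenario 4). This is a weighting effect. With one working factor, the false-signal rate for the inert factor is about 16% against about 5%, with no average bias.

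The assumptions are equal weights as the target, the 0.025 to 0.975 cut-offs, the mirrored version of scenario 6, N=1500, no time buckets and a normal approximation to the posterior. The reduced enrolment of 1,281 was not simulated. Under the global null there is little harm. The primary arm-vs-STS analysis and the 0.991 rule are unaffected.

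**What to change.** In SAP 8.9.2, report component effects as equal-weight contrasts of the model (1) posterior, on the log odds scale:
- RPM-Low vs STS = theta1 + theta3/2
- RPM-High vs STS = theta1 + theta2 + (theta3 + delta)/2
- RPM-High vs RPM-Low = theta2 + delta/2
- Standard vs STS = theta1 + theta2/2
- Enhanced vs STS = theta1 + theta3 + (theta2 + delta)/2
- Enhanced vs Standard = theta3 + delta/2

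Correct the labels on theta1 and theta1+theta2. If model (3) is kept, call it an allocation-weighted summary and do not use it to say which component works. The same contrasts are advisable for the pooled team comparison in 8.10.2.

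Model (1) is fitted anyway, so only SAP wording changes. One cost is precision. From the cell sizes, the ratio of standard errors for High vs Low is √[¼Σ(1/n) ÷ (1/(n1+n3) + 1/(n2+n4))]. This is √(0.00556/0.00482) = 1.07 in scenario 3 and √(0.00673/0.00560) = 1.10 in scenario 4, so about 7 to 10% wider. The other cost is a small residual bias from adaptive randomization: 1.26 against 1.225 for High vs Low in scenario 3, and 1.19 against 1.225 for RPM-High vs STS in the mirrored scenario 6, where model (3) gave 1.34.

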### 8.9.3. Final analysis of mortality and PDHD among survivors

Analysis of mortality and PDHD among survivors will be conducted jointly via the model in Section 8.5.2. This model relaxes the proportional odds assumption, allowing for the effect of interventions on mortality to be independent of the effect on PDHD among survivors. From this model, we will estimate the following posterior probabilities:

- Posterior probability of superiority of each active arm over STS with respect to probability of survival to 90 days
- Posterior probability that each active arm is superior to the other active arms with respect to probability of survival to 90 days
- Posterior probability of superiority of each active arm over STS with respect to PDHD among survivors
- Posterior probability that each active arm is superior to the other active arms with respect to PDHD among survivors

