### 8.3.2. Bayesian ordinal logistic regression

The primary analysis employs a Bayesian cumulative logistic regression assuming proportional odds effects. Let  $Y_i \in \{-1, 0, 1, \dots, 89, 90\}$  be the primary ordinal 90-day home days endpoint for patient  $i$ . Let  $\gamma_{ij}$  denote the probability of patient  $i$  observing a home days endpoint of  $j$  or lower. For  $j = -1, \dots, 89$ , the primary analysis model is formulated as:

$$\begin{aligned} \text{logit}(\gamma_{i,j}) &= \alpha_j - (X_{i1}(\theta_1 + \theta_2 X_{i2} + \theta_3 X_{i3} \\ &\quad + \delta X_{i2} X_{i3}) + \beta_1 Z_{i1} + \beta_2 Z_{i2} + W_{i,COV} \boldsymbol{\kappa}) \end{aligned} \quad (1)$$

where  $\text{logit}(\gamma_{ij}) = \log\left(\frac{\gamma_{ij}}{1-\gamma_{ij}}\right)$  are the log odds of the probability that  $Y_i$  is less than  $j$ . The variables,  $X_{i1}, X_{i2}, X_{i3}$ , are indicators for treatment assignment, where  $X_{i1} = 1$  when randomized to one of the 4 care model interventions (interventions 2-5 above) and 0 when randomized to the STS arm,  $X_{i2} = 1$  when randomized to an intervention with RPM high and  $X_{i2} = 0$  for RPM low,  $X_{i3} = 1$  when randomized to an intervention with enhanced team and  $X_{i3} = 0$  for standard team. The model is formulated such that STS is considered the referent treatment and all parameters learned in the model are in relation to STS. The four care models are modeled as a factorial comprised of the level of RPM and type of team deployed.

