### 8.5. Proportional odds assumption

The ordinal logistic regression model assumes that the effect of a treatment on the odds of higher PDHD is the same for all levels of the outcome. For example, this assumption entails that the effect of an intervention on the odds of surviving through the 90-day post discharge period increases by an amount proportional to the odds of having greater than 80 PDHD. In the event that the interventions have no effect on survival, but a beneficial effect on PDHD among survivors, the proportionality assumption will be violated.

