#### 8.5.2. Extending the proportional odds model

To assess the proportional odds assumption around the lower end of the distribution, we propose the following non-proportional model in Equation (2):

$$\text{logit}(\gamma_{i,j}) = \alpha_j - (X_{i1}(\theta_{1,k} + \theta_{2,k}X_{i2} + \theta_{3,k}X_{i3} + \delta_kX_{i2}X_{i3}) + \beta_1Z_{i1} + \beta_2Z_{i2} + W_{i,COV} \boldsymbol{\kappa}), \quad k = -1, \geq 0. \#(2)$$

where we allow the treatment effect to vary for death ( $k = -1$ ) and stay constant across the home-days distribution (0-90). The effects for strata are constant across the full scale, -1:90.

This proposed model results in the probability of death for patients on STS equal to:

$$\Pr(Y_i = -1) = \text{logit}^{-1}(\alpha_{-1} - (\beta_1Z_{i1} + \beta_2Z_{i2} + W_{i,COV} \boldsymbol{\kappa}))$$

And the probability of death for patients on a treated arm:

$$\Pr(Y_i = -1) = \text{logit}^{-1}(\alpha_{-1} - (X_{i1}(\theta_{1,-1} + \theta_{2,-1}X_{i2} + \theta_{3,-1}X_{i3} + \delta_{-1}X_{i2}X_{i3}) + \beta_1Z_{i1} + \beta_2Z_{i2} + W_{i,COV} \boldsymbol{\kappa})).$$

Then the remainder of the 90-day home days scale can be described using the usual proportional odds shift, for

$j = 1, \dots, 89$ :

$$\Pr(Y_i \leq j) = \text{logit}^{-1}(\alpha_j - (X_{i1}(\theta_{1,\geq 0} + \theta_{2,\geq 0}X_{i2} + \theta_{3,\geq 0}X_{i3} + \delta_{\geq 0}X_{i2}X_{i3}) + \beta_1Z_{i1} + \beta_2Z_{i2} + W_{i,COV} \boldsymbol{\kappa})).$$

The priors will be the same as specified in Section 8.3.3 for each level of the log-odds treatment effects,  $\theta_k$ .

The qualitative interpretation of this model will be similar to the primary analysis model above; however, this formulation will allow us to assess how these interventions impact mortality versus the time at home.

Analyses of mortality and PDHD among survivors from the model in equation (2) will be considered separate secondary analyses. See Section 8.9.3 below.

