## 12.6 Operating characteristics when assumptions are violated

As noted in Section 8.5, it is possible that the interventions have differential effects on patients who would have died within 90 days had they been assigned to SRS compared to those who would have survived. This type of differential effect of treatment for different types of patients violates the proportional odds assumption from the ordinal logistic regression model. Therefore, we provide operating characteristics for simulations in which patient data are generated under non-proportional assumptions. In these scenarios, we leave the probability of death unchanged regardless of the treatment effect and shift the remaining portion of the home-days endpoint (0-90) by the scenario specific OR. See Figure 2 for a visual representation of the treatment effect on the baseline probability distribution under these non-proportional assumptions.

Table 6 shows the population characteristics under a range of odds ratios for these two scenarios, for each of the 3 population subsets. Odds ratios in Table t reflect the effect of interventions on home days among survivors only.

**Table 6. Summary of PDHD distribution under different treatment effect scenarios\*, when proportionality of effect of intervention is violated**

|                      | Median PDHD
Among
Survivors
(IQR) | Probability
of
Mortality | Probability
of
90 PDHDs |
|----------------------|--------------------------------------------|--------------------------------|-------------------------------|
| OR=1.00       |                                            |                                |                               |
| Baseline             | 90 (82, 90)                                | 0.13                           | 0.45                          |
| Severe               | 88 (79, 90)                                | 0.17                           | 0.38                          |
| Discharged
to SNF | 84 (70,90)                                 | 0.30                           | 0.23                          |
| OR=1.25       |                                            |                                |                               |
| Baseline             | 90 (84, 90)                                | 0.13                           | 0.50                          |

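### Equation (2) cannot separate the mortality effect from the home-days effect among survivors, and reports a false survival benefit when only survivors gain days

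*Combined protocol and SAP*

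**What the plan says.** SAP 8.3.2 codes death as −1 and works with γ_ij, the probability of patient i "observing a home days endpoint of" j or lower. Section 8.5 names the departure from proportional odds that it has in mind: "In the event that the interventions have no effect on survival, but a beneficial effect on PDHD among survivors".

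The response is Equation (2) in 8.5.2, "where we allow the treatment effect to vary for death", with a second, common treatment effect for levels 0 to 90. The intercepts α_j are shared, and the stated purpose is that "this formulation will allow us to assess how these interventions impact mortality versus the time at home".

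Section 8.9.3 then makes this the inferential model: "Analysis of mortality and PDHD among survivors will be conducted jointly via the model in Section 8.5.2". Four sets of posterior probabilities are read from it: survival and survivor home days, each against STS and among the active arms. The justification is that the model works by "allowing for the effect of interventions on mortality to be independent of the effect on PDHD among survivors".

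Section 12.6 simulates the same departure by another rule: "we leave the probability of death unchanged regardless of the treatment effect and shift the remaining portion of the home-days endpoint".

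**The concern.** Every cumulative probability for j ≥ 0 in Equation (2) still counts the deaths, so θ(≥0) is not an effect among survivors. Cumulative probabilities must also increase with j. In a treated patient this ties θ(≥0) to θ(−1) through the distance between the two lowest intercepts, and that distance is very small because almost no survivor has close to zero home days. The two effects cannot then be independent.

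Mortality is a listed secondary endpoint, and no other inferential model is given for it or for home days among survivors. The protocol (Measures, Primary outcome) expects little effect on time to death, so the scenario that breaks the model is a plausible one for this trial. The risk is a reported survival benefit that does not exist, together with a diluted home-days effect.

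**Working it through.** **Inputs.** Table 2 (12.2), also the prior weights in 8.3.3: death 0.133; 0–19 0.005; 20–39 0.017; 40–49 0.017; 50–59 0.026; 60–69 0.042; 70–79 0.077; 80–89 0.228; 90 0.454. These sum to 0.999 and are rescaled to 1. The 92-level version spreads each band evenly over its days, as 8.3.3 does. Strata are 11% severe (OR 0.75) and 37% SNF (OR 0.35), from 12.2. Arm sizes come from Table 7.1. An odds ratio above 1 means benefit.

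**Step 1: reproduce Table 6 (baseline, OR 1.5).** Hold deaths at 0.133 and shift the odds among survivors. P(90 | alive) = 0.454/0.866 = 0.524, odds 1.102; × 1.5 = 1.653, probability 0.623; × 0.867 = 0.540. Table 6 gives 0.54 with mortality 0.13. All 12 rows of Table 6 reproduce this way within rounding. Equation (2) with θ(−1) = 0 gives a different figure: odds 0.454/0.545 = 0.833; × 1.5 = 1.250; probability 0.555. So 12.6 generates data from a model conditional on survival, which is not Equation (2).

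**Step 2: the constraint.** A treated patient needs P(Y ≤ −1) < P(Y ≤ first survivor level), that is

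θ(≥0) − θ(−1) < α_0 − α_−1.

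On nine levels the right side is logit(0.1381) − logit(0.1331) = −1.831 + 1.874 = 0.043. With no mortality effect the largest admissible home-days OR is exp(0.043) = 1.04; on 92 levels it is 1.002. At OR 1.5 with θ(−1) = 0, P(Y ≤ 19) = 0.0965 while P(death) = 0.1331, so P(0–19 days) = −0.037. These values have no valid likelihood.

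**Step 3: what the fit converges to.** Equation (2) was fitted by maximising the expected log-likelihood for STS against one active arm.

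| Truth | Setting | Fitted survival OR | Fitted home-days OR |
|---|---|---|---|
| Deaths equal, survivor OR 1.25 | 9 levels, baseline | 1.16 | 1.17 |
| Deaths equal, survivor OR 1.5 | 9 levels, baseline | 1.30 | 1.32 |
| Deaths equal, survivor OR 1.5 | 92 levels, baseline | 1.325 | 1.326 |
| Deaths equal, survivor OR 1.5 | strata mix of 12.2 | 1.26 | 1.28 |
| Deaths equal, survivor OR 1.75 | 9 levels, baseline | 1.44 | 1.47 |
| Mortality OR 1.5, survivors unchanged | 9 levels, baseline | 1.17 | 1.15 |

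In the second row, fitted mortality is 14.8% (STS) against 11.8% (treated); both are truly 13.3%. The last row shows the leak in the other direction: a real mortality effect is diluted and a home-days effect appears.

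**Step 4: posterior probabilities.** Equation (2) with the planned priors was run on 300 simulated two-arm trials per case (baseline stratum, nine levels, no calendar-time terms). There is no mortality effect in any case. Section 8.9.3 sets no threshold, so three are shown.

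| Survivor OR (STS v arm) | Mean Pr(survival benefit) | >0.95 | >0.975 | >0.991 |
|---|---|---|---|---|
| 1.25 (450 v 376) | 0.80 | 28% | 18% | 9% |
| 1.5 (450 v 472) | 0.94 | 68% | 57% | 39% |
| 1.75 (450 v 556) | 0.99 | 92% | 88% | 75% |
| 1.5 (375 v 393) | 0.92 | 61% | 52% | 37% |

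The last row scales to 1,281 × 0.975 ≈ 1,249 complete patients. In the 450 v 472 trials at OR 1.5, a separate binomial model for death gave a mean of 0.50 and exceeded 0.95 in 4% of trials. Monte Carlo error is about 3 percentage points.

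**The case against.** The algebra is not in dispute; the case on the other side concerns reach and size.

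- **Secondary only.** Equation (2) drives neither the adaptive randomisation, the futility rule nor the 0.991 success threshold, and 8.9.3 attaches no decision rule. This stands, but the model is still the only planned inference on mortality.
- **Harmless when the effects agree.** Equation (2) contains model (1). In large samples it returns 1.00/1.00 under the null and 1.50/1.50 under a proportional OR of 1.5. This stands too: the bias appears when the effects differ, which is the situation the model was added for.
- **Stan would reject invalid draws.** It would, so the output would contain no negative probabilities. Rejection pushes θ(−1) up towards θ(≥0), and that is what creates the false survival benefit.
- **Section 8.5.1 gives an unaffected check.** The odds ratio dichotomised at death would show about 1.0. It is a plot for visual inspection and does not replace the 8.9.3 probabilities.
- **Merging sparse levels (8.3.4).** This does not rescue the model. About 0.005 × 1,249 = 6 patients are expected at 0–19 days, so the gap to the first occupied level stays small.
- **The size rests on Table 2.** Those data come from patients described in 12.1 as low risk, while the trial enrols medium and high risk. If 1.5%, 3% or 5% of patients fell in 0–19 days (assumed values, taken from the 90-day level; nine levels), the false survival OR would be 1.27, 1.23 or 1.19. The size is therefore a range; the direction does not change.

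**Conclusion.** The concern holds. Equation (2) cannot represent the effects that 8.9.3 says it estimates, and the scenario named in 8.5 lies outside its parameter space.

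For a true survivor OR of 1.5 and no mortality effect, the false survival OR is about 1.30 on the Table 2 distribution, 1.26 with the strata mix, and 1.19 to 1.27 under the heavier lower tails assumed above. With 450 v 472 patients the posterior probability of a non-existent survival benefit averages 0.94. These figures assume the Table 2 shape; the posterior simulation also leaves out strata and time terms. The constraint itself depends on none of these simplifications.

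Tables 7.1 and 7.2 give one odds-ratio bias per arm, as a single-effect model such as model (1) would, so the plan contains no operating characteristics that would have exposed the problem.

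**What to change.** Replace Equation (2) in 8.5.2 with a two-part model and refer 8.9.3 to it:

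1. logistic regression for death, Pr(Y = −1);
2. a cumulative logit for Pr(Y ≤ j | Y ≥ 0), j = 0 to 89, among survivors.

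Each part has its own arm, interaction, strata and time-bucket terms, with the 8.3.3 priors on those coefficients. Read the survival probabilities from part 1 and the survivor home-days probabilities from part 2.

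The intercept priors need a sentence. The Dirichlet in 8.3.3 splits into a Beta with weights 0.133 and 0.866 for death against survival, and a Dirichlet over 0–90 with the remaining weights (or those weights rescaled to sum to 1).

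In addition:

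- State that part 2 conditions on a post-randomisation event, and carry over the survivor-selection caution already given in 8.9.5.
- Correct the lower part of 8.5.2, which starts at j = 1 and leaves j = 0 undefined.
- Report operating characteristics for the two-part model under the Table 6 scenarios.

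The cost is revised wording in 8.5.2 and 8.9.3, a simpler Stan program and one set of simulations. No new data are needed, and the primary analysis, randomisation and futility rules do not change.
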